### Sample size calculation

GWG was used as primary outcome for the sample size calculation, because healthy GWG is discussed with all expectant mothers participating in the lifestyle intervention. The brief lifestyle intervention is assumed to reduce the proportion of study participants with excessive gestational weight gain by 10%. Similar interventions have achieved a reduction in the proportion of excessive weight gain of around 20% [18, 59]. The target was set lower in this study, because the lifestyle intervention is implemented in a routine health service setting with less stringent inclusion criteria. To detect a 10% reduction in excessive gestational weight gain with a power of 80%, an alpha of 0.05 and an ICC of 0.05 a sample of *n* = 1240 pregnant women is required. This number was increased to *n* = 1860 to account for a drop-out rate of 25% in the intervention group and a 40% drop-out rate in the control group (see Fig. 1).

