## Methods/design

### Study design

A hybrid effectiveness-implementation trial (Type II) is being used to simultaneously collect data on the effectiveness and implementation of the GeMuKi lifestyle intervention [31, 32]. This design was selected because there is strong evidence that interventions during pregnancy can effectively improve lifestyle-related risk factors, research indicates that lifestyle counseling during routine check-up visits is feasible in Germany and evidence on implementation of lifestyle interventions during pregnancy is scarce. The GeMuKi intervention comprises various components previously identified to enhance lifestyle counseling during pregnancy. To our knowledge, effectiveness of these components has not been evaluated in combination, yet.

The trial has two arms (see Fig. 1). In the intervention arm gynecologists, midwives and pediatricians carry out the GeMuKi lifestyle intervention during routine prenatal visits and infant check-ups. In the control arm they provide care as usual. The study takes place in both urban and rural areas within the German state Baden-Wuerttemberg. To reduce discrepancies between study regions intervention and control regions were matched into pairs using propensity score matching. Matching was conducted immediately after the project kick off in October 2017 to provide enough time for enrollment of multi-professional providers and for conducting implementation training in the intervention regions before commencing recruitment of study participants. Matching was based on average income per capita, the number of births among persons insured by BARMER (i.e. the statutory health insurer agreeing first to participate in the GeMuKi project) and the number of gynecologists in the study regions. This resulted in four matched study region pairs, which were randomized into intervention and control regions.

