### Challenges and limitations

Execution of this study protocol involves several challenges. Embedding the GeMuKi intervention into routine care may pose a challenge for providers, who already have limited time during busy patient schedules [61]. To support providers in conducting the lifestyle counseling efficiently and as planned, the GeMuKi-Assist Counseling Tool includes various supports for providers, such as example questions to discuss with women.

Detecting expected effects of the GeMuKi intervention will require a large sample size. To address this challenge, multiple recruitment strategies will be used. To encourage intervention uptake by multi-professional providers the research team will involve regional opinion leaders among professional groups. Additionally, a relatively high drop-out rate was assumed in the power calculation.

An intervention provided in health service settings can only have a limited impact on individual lifestyle behaviors. Important other determinants in the social, physical and economic environment are not directly addressed by the GeMuKi intervention. Study participants can only be referred to additional supports and resources available in the community. Hence, the GeMuKi intervention can only be one element in an integrated, system wide approach required for successful obesity prevention.

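### The 80% power stated for 1240 women does not allow for randomisation of only eight regions; it holds only if residual between-region variance is near zero and large-sample critical values are used

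*Protocol article*

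**What the plan says.** Under Study design, regions were propensity-matched into pairs on income, insured births and number of gynecologists: "This resulted in four matched study region pairs, which were randomized into intervention and control regions". The Abstract confirms eight regions, so there are four per arm.

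Under Sample size calculation, the intervention is assumed to "reduce the proportion of study participants with excessive gestational weight gain by 10" per cent. The article then gives the requirement: "with a power of 80%, an alpha of 0.05 and an ICC of 0.05 a sample of" 1240 women. This is raised to 1860 "to account for a drop-out rate of 25% in the intervention group and a 40% drop-out rate in the control group". The paragraph does not mention the eight regions or the matching, and it does not say at which level the ICC applies. Data analyses specifies mixed effects models for the clustered data without naming the clusters. Challenges and limitations notes that "Detecting expected effects of the GeMuKi intervention will require a large sample size"; it does not mention the number of regions.

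**The concern.** When regions are allocated, the precision of the treatment comparison is limited by how much regions differ and by how many there are. A calculation that inflates only for clustering within practices leaves out the variance component that belongs to the randomised unit. It also uses critical values suited to many independent clusters, when there are eight.

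The Discussion says the results are meant to inform a federal decision on roll-out and public funding. If the effect estimate is inconclusive, a reader who trusts 80% power may take it as evidence that the intervention does not work. With an ordinary amount of region-to-region variation the design may have had well under that chance of detecting the assumed effect.

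**Working it through.** **Inputs from the article:** power 80%; alpha 0.05; ICC 0.05; 1240 evaluable women, hence 620 per arm; 8 regions, 4 per arm, hence 1240/8 = 155 women per region if equal.

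**Assumptions:** two-sided test; 10% means 10 percentage points; control rate 30-60%, because none is stated. A 10% relative reduction cannot be the basis: 50% to 45% already needs 3130 women before any clustering.

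**Step 1. The drop-out inflation reproduces.** 620/0.75 + 620/0.60 = 826.7 + 1033.3 = 1860. This also confirms 620 evaluable women per arm.

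**Step 2. What reproduces 1240?** Unclustered n per arm = [1.96√(2p̄(1−p̄)) + 0.8416√(p₁(1−p₁) + p₂(1−p₂))]² / d². For 45% versus 35%: (1.358 + 0.580)² / 0.01 ≈ 376. The implied design effect is 620/376 = 1.65. From DE = 1 + (m − 1) × 0.05, m = 1 + 0.65/0.05 = 14 women per cluster, or about 1240/14 ≈ 89 clusters.

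| Control rate | n per arm, unclustered | Implied DE | Implied women per cluster |
|---|---|---|---|
| 30% | 294 | 2.11 | 23 |
| 40% | 356 | 1.74 | 16 |
| 45% | 376 | 1.65 | 14 |
| 50% or 60% | 388 | 1.60 | 13 |

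Allowing also for control rates down to 20%, a one-sided test or a continuity correction, the implied size ranges from 11 to 60. It never reaches 155. The figure fits practice-sized clusters with no region component.

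**Step 3. If ICC 0.05 applied to regions.** DE = 1 + 154 × 0.05 = 8.7, so effective n = 620/8.7 ≈ 71 per arm. At 45% versus 35%, v = 0.45 × 0.55 + 0.35 × 0.65 = 0.475 and SE = √(0.475 × 8.7/620) = 0.0816. Power = Φ(0.10/0.0816 − 1.96) = 23%, or 18% with a noncentral t on 6 df. With unlimited women per region, SE tends to √(v × 0.05/4) = 0.0771, and power to 25% (normal).

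| Control rate | Normal | t, 6 df | Ceiling, unlimited women (normal) |
|---|---|---|---|
| 30% | 28% | 22% | 31% |
| 45% | 23% | 18% | 25% |
| 60% | 22% | 17% | 25% |

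These figures credit no gain from matching.

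**Step 4. If ICC 0.05 applies to practices.** Add a residual region ICC ρ, meaning what remains after matching: SE² = (v/620) × 1.65 + vρ/4, with v = 0.475 (45% versus 35%). At ρ = 0, SE = √0.001264 = 0.0356 and power = Φ(2.81 − 1.96) = 80%, which is the article's own figure. At ρ = 0.01, SE = √(0.001264 + 0.001188) = 0.0495 and power = Φ(2.02 − 1.96) = 52%. The values of ρ are assumptions.

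| Residual region ICC | Normal | t, 6 df (unpaired) | t, 3 df (four pairs) |
|---|---|---|---|
| 0 | 80% | 65% | 49% |
| 0.005 | 64% | 49% | 36% |
| 0.01 | 52% | 40% | 29% |
| 0.02 | 38% | 29% | 22% |

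**The case against.** The strongest reply is that the article never places the 0.05 at region level, and that the back-calculation itself points to practices, where 1240 reproduces exactly. That stands. A reader might infer from Step 3 that the trial has about 20-odd per cent power and that no number of women could reach 80%. The article does not support that as an unconditional statement. It applies only if 0.05 is the region ICC and matching gains nothing.

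Matching is a fair second point. The regions were paired to reduce differences between them, and the sample size paragraph takes no credit for this. For 50% versus 40% with region ICC 0.05 and unlimited women, matching would have to remove about 79% of the between-region variance to reach 80% by the normal approximation. The article claims no such gain. Analysing the pairs also leaves 3 df, so 6 df cannot be prescribed as the only reference.

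Third, a condensed article may leave cluster sizes and degrees of freedom to a fuller document. That is so, and their absence is not the point. The point is that a stated 80% is set beside a stated allocation of eight regions, and no later document changes how many regions were randomised. Nor do mixed models supply power: including region limits precision to eight units, and omitting it ignores the unit of allocation.

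Finally, a reader might take Challenges and limitations to offer more women as the cure for few regions. It does not. It describes a recruitment challenge and how recruitment will be supported.

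**Conclusion.** The concern holds in conditional form. The 80% is reached only if the residual region-level variance is essentially zero and large-sample critical values are used. With ICC 0.05 at practice level and 45% versus 35%, a residual region ICC of only 0.01 lowers power to about 52% (normal) or 40% (6 df), and it is lower again on 3 df. With ICC 0.05 at region level, power is about 22-28% (normal) or 17-22% (6 df), and without a matching gain it stays at or below about 31% (normal) however many women enrol.

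This rests on a 10-point effect, a two-sided test, equal region sizes, an assumed control rate of 30-60% and assumed region ICCs. The control rate moves the figures but not the conclusion; even at 20% versus 10% the region-level ceiling is 43% (normal). That the calculation set region variance to zero is inferred from the size of 1240; the article does not say so. The drop-out inflation to 1860 is correct.

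**What to change.** In Sample size calculation, replace the unconditional 80% with the power, or the detectable difference, that 620 evaluable women per arm give over residual region ICCs of 0 to 0.02. State whether the ICC of 0.05 refers to practices or regions, the assumed control rate, and that the 10% is in percentage points if that is what was meant. Use a small-sample reference that matches the planned analysis: 6 df if unpaired, 3 df if the four pairs are analysed. If a detectable difference is reported, say which reference distribution it uses.

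In Challenges and limitations, add that precision is bounded by eight randomised regions.

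The cost is one reworded paragraph, a short table and one sentence. No extra participants or change of design are needed. The downside is a less favourable stated power.

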### Data analyses

The data entry fields in the GeMuKi-Assist Counseling Tool and electronic surveys collected through the GeMuKi-Assist App are predefined to allow for plausible data only. Additional plausibility checks will be performed before commencing data analysis. Analyses of these quantitative data using descriptive statistics, statistical tests and regression models will be conducted in SPSS and R. Analyses for all primary and secondary outcomes will follow an intention-to-treat principle, which compares the intervention arm to the control arm, without regard to intervention completion or compliance. Mixed effects models will be used to account for the clustered structure of the data. Multiple imputation methods will be used to deal with missing values. Exploratory analyses will be performed to explore intervention outcomes for subgroups of study participants, e.g. according to SES and migration background.

All focus groups and interviews will be audio-recorded and transcribed verbatim. Qualitative analysis of focus groups, interviews and documents will be carried out in MAXQDA using a framework analysis approach [60]. Two multidisciplinary researchers will conduct coding independently and discuss discrepancies. The principle of triangulation will be applied continuously to test validity through comparing information from different data sources.

To provide a better understanding of the overall process of implementation and gain insights into possible interactions between implementation and effectiveness of the GeMuKi intervention the research team will conduct integrated data analyses combining qualitative and quantitative data sources.

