Finally, the GeMuKi lifestyle counseling will be provided continuously over an 18-month period. This is in line with previous research findings, demonstrating that longer duration of lifestyle interventions result in more effects [74, 75].

The GeMuKi intervention will be evaluated in eight regions of the German state Baden-Wuerttemberg. To support implementation as planned, a comprehensive implementation strategy has been developed. It includes a training curriculum and funding scheme, which can be scaled up, in case the intervention proves to be effective. This evaluation study is designed to provide insights for policy makers at the German Federal Joint Committee (G-BA), who will decide about roll-out and public funding of the intervention on a federal scale.

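### Eight regions were randomised, but the sample size fits only practice-sized clusters and the analysis text does not say that the mixed model carries region

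*Protocol article*

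**What the plan says.** Three sections of the protocol article bear on this.

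- **Study design.** Regions were paired by propensity score before allocation: "To reduce discrepancies between study regions intervention and control regions were matched into pairs using propensity score matching". Then: "This resulted in four matched study region pairs, which were randomized into intervention and control regions". The randomised unit is therefore the region, four per arm, and the Discussion confirms the count: "The GeMuKi intervention will be evaluated in eight regions of the German state Baden-Wuerttemberg".
- **Sample size calculation.** The intervention is assumed to "reduce the proportion of study participants with excessive gestational weight gain by 10" per cent, and "with a power of 80%, an alpha of 0.05 and an ICC of 0.05 a sample of *n* = 1240 pregnant women is required". The section does not give the level of the ICC, a cluster size or a control rate, and it does not say whether the 10% is absolute or relative.
- **Data analyses.** "Mixed effects models will be used to account for the clustered structure of the data". No random-effect level, pair term or reference distribution is named.

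Women are recruited through gynecologist practices, so practices form a second level of clustering inside the regions.

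**The concern.** The level at which chance was introduced is the region. A valid comparison of the arms has to measure the effect against variation between regions, and only eight regions supply that information. If the model has a random effect for practice only, any real difference between regions in population or local care is read as an intervention effect, and the standard error is too small. If region is included but the test uses a normal reference, the standard error rests on very few clusters and the p-value can still be too small.

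The article's Discussion says the results are meant to inform a federal decision on roll-out and public funding. A false positive would be costly there.

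The short analysis sentence alone would be ordinary brevity for an article. The sample size raises the question, because it points to a cluster level below the one randomised.

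**Working it through.** **1. Reproduce the plan's figures.** The 1240 is 620 per arm. With the stated drop-out, 620/0.75 + 620/0.60 = 826.7 + 1033.3 = 1860. This agrees exactly with the article. The 1240 itself cannot be reproduced, because control rate and cluster size are not given.

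**2. Which cluster size does 1240 imply?** Assumptions: two-sided 5%, 80% power, pooled-variance formula for two proportions without continuity correction, 10-point absolute reduction. With design effect DE = 1 + (m − 1) × 0.05, the implied cluster size is m = 1 + (620/n − 1)/0.05, where n is the unclustered number per arm.

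| Control vs intervention | n per arm | DE = 620/n | implied m |
|---|---|---|---|
| 30% vs 20% | 294 | 2.11 | 23.2 |
| 40% vs 30% | 356 | 1.74 | 15.8 |
| 50% vs 40% | 388 | 1.60 | 13.0 |
| 60% vs 50% | 388 | 1.60 | 13.0 |

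A relative 10% reduction does not fit: 50% vs 45% needs 1565 per arm before any allowance for clustering.

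**3. Could the cluster be the region?** Evaluable women per region: 1240/8 = 155. DE = 1 + 154 × 0.05 = 8.7, and the effective size per arm is 620/8.7 = 71. Power for a 10-point reduction is then about 22 to 28% over control rates of 30 to 60%, even with a normal reference. With four clusters per arm the effective size cannot exceed 4/0.05 = 80 per arm, however many women are recruited. So an ICC of 0.05 at region level is incompatible with 80% power.

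**4. Type I error if region is omitted.** Assumptions: m = 13, correlation 0.05 within a practice, correlation r between women of the same region in different practices (r is not in the article). The true variance exceeds the assumed variance by f² = [1.60 + (155 − 13) × r]/1.60, and the error is 2 × [1 − Φ(1.96/f)].

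| Region ICC r | f | Type I error | Simulated |
|---|---|---|---|
| 0 | 1.00 | 5.0% | 5.3% |
| 0.002 | 1.09 | 7.1% | 7.2% |
| 0.005 | 1.20 | 10.3% | 10.7% |
| 0.01 | 1.37 | 15.4% | 16.5% |
| 0.02 | 1.67 | 23.9% | 25.2% |

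The simulation used 40,000 balanced trials per setting with a Gaussian outcome (8 regions, 12 practices each, 13 women per practice) and did not model the pairing. With m = 23 the formula gives 5.0% at r = 0 and 19.2% at r = 0.02. For scale, at an event rate of 40% a region ICC of 0.005 is a between-region SD of √(0.005 × 0.4 × 0.6) = 3.5 percentage points, and 0.02 is 6.9 points.

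**5. Type I error if region is modelled with a normal reference.** The same simulation with a REML region effect gives 4.0%, 6.7%, 8.1%, 9.0% and 9.9% at region ICC 0, 0.005, 0.01, 0.02 and 0.05. The limiting value is P(|t₆| > 1.96) = 9.8%.

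**6. With a small-sample reference.** A t test of region means on 6 df holds 4.9 to 5.2% over region ICC 0 to 0.05. A REML region effect with 6 df gives 1.2 to 5.1%, so it is conservative when regions hardly differ.

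**The case against.** The strongest reply is that this is a journal article. Random-effect levels and degrees of freedom are commonly left to a full protocol or analysis plan, which is not shown. The mixed-model sentence is compatible with a region effect, and nothing says that a normal reference will be used. A sample size worked out at one level also does not fix the levels of the model. All of this stands, so a reader who infers that the plan leaves region out goes further than the text.

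A reader might also infer that the true type I error is 10 to 25%. The document does not support that either. Such a range needs region to be omitted and a region ICC of roughly 0.005 to 0.02, and no region ICC is stated. At 0 to 0.002 the error is 5 to 7%. Matching on income, births and number of gynecologists was meant to reduce regional differences, and the calculations do not credit it. If region is modelled, the error stays within about 4 to 10%.

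What the reply does not remove is the mismatch inside the article. Regions were randomised, the only clustering quantified cannot be regional, and the analysis sentence does not say which of the two levels it means.

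**Conclusion.** The point holds as a conditional one. The article randomises eight regions, its sample size fits only practice-sized clusters (about 13 to 23 women, given a 10-point absolute reduction and control rates of 30 to 60%), and the analysis text does not tie the model to the randomised unit. Two cases must be kept apart:

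- **Region omitted:** type I error about 5 to 25% for an assumed region ICC of 0 to 0.02.
- **Region modelled, normal reference:** about 4 to 10%.

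Both ranges rest on balanced clusters and take no account of the pairing. The first also depends on a region ICC that the article does not supply. The document does not show that either analysis will be used. It does leave both open in a trial with four clusters per arm.

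**What to change.** State in the analysis section, before outcome data are analysed by arm, that region is the randomised cluster in the primary analysis. Two standard forms would do:

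- a mixed model with random effects for region and for practice within region, with a small-sample degrees-of-freedom correction; or
- a two-stage analysis: an individual-level model without the arm term, then a comparison of region-level residuals between arms.

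Say in advance whether the pairs are modelled. If they are not, the t reference has about 6 df (8 − 2). If the analysis is paired, it has 3 df (4 − 1). An exact test within pairs would not serve as the primary test at 5%: four pairs allow 2⁴ = 16 allocations, so its smallest two-sided p-value is 2/16 = 0.125. Report results for all eight regions, and state the level and cluster size to which the ICC of 0.05 refers.

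The change takes a few lines and no new data. The price is precision. For the same standard error, the interval widens by 2.447/1.96 = 1.25 with 6 df and 3.182/1.96 = 1.62 with 3 df. Power also falls below the stated 80%. For 50% vs 40% with m = 13, the noncentrality is 0.10/√[(0.25 + 0.24)/620 × DE]. With no regional variation (DE = 1.60) it is 2.81, which gives about 65% power on 6 df and 49% on 3 df. At a region ICC of 0.01 (DE = 1.60 + 142 × 0.01 = 3.02) it is 2.05, which gives about 41% and 30%. The 3 df figures assume that matching gains nothing; effective matching would raise them.

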## Discussion

This study will evaluate a brief counseling intervention to reduce lifestyle-related risk factors of overweight and obesity among expectant mothers and their infants. The GeMuKi intervention is innovative, as it combines several components that have been identified to enhance lifestyle counseling during pregnancy.

First, the lifestyle counseling is integrated into routine prenatal visits and infant check-ups. This puts a smaller burden on participants than add-on approaches [61] and provides a low threshold approach to reach expecting mothers and their infants. According to most recent estimates almost 90% of expecting mothers in Germany regularly attend prenatal visits [62] and over 95% of infants attend infant check-ups during the first year of life [63].

Second, lifestyle counseling is tailored to individual intervention participants. A tailored approach that recognizes individual differences in motivation, knowledge, needs and circumstances is recommended, because one-size fits all approaches have shown to be less effective in preventing overweight and obesity [61, 64]. The GeMuKi intervention consists of a series of brief counseling sessions using MI techniques. MI is a person-centered counseling approach, which encourages active involvement of intervention participants in the behavior change process. As evidenced by systematic reviews, MI has effectively promoted different health behaviors [65, 66] and has been associated with lifestyle changes in the long-term [67].

Third, providers implementing the GeMuKi intervention, will receive training in applying MI techniques. This will address needs expressed by professionals providing pre- and postnatal care to improve communication skills to discuss the sensitive topic of obesity and gestational weight gain [68–71].

Fourth, lifestyle counseling in the GeMuKi intervention will be supported by the novel telehealth platform GeMuKi-Assist. It includes a counseling tool for documentation and collaboration between multi-professional providers, an App for study participants with supporting information to encourage attainment of lifestyle change goals and a study monitor to support the evaluation study. An increasing body of evidence suggests that when used as an adjunct to face-to-face counseling methods computer and communication technology can be an effective tool to achieve lifestyle behavior changes, also among women with lower socio-economic status [72, 73].

Finally, the GeMuKi lifestyle counseling will be provided continuously over an 18-month period. This is in line with previous research findings, demonstrating that longer duration of lifestyle interventions result in more effects [74, 75].

The GeMuKi intervention will be evaluated in eight regions of the German state Baden-Wuerttemberg. To support implementation as planned, a comprehensive implementation strategy has been developed. It includes a training curriculum and funding scheme, which can be scaled up, in case the intervention proves to be effective. This evaluation study is designed to provide insights for policy makers at the German Federal Joint Committee (G-BA), who will decide about roll-out and public funding of the intervention on a federal scale.

